## Abstract

**Introduction:**

It has been suggested that removal of proinflammatory substances that accumulate in stored donor red cells by mechanical cell washing may attenuate inflammation and organ injury in transfused cardiac surgery patients. This trial will test the hypotheses that the severity of the postoperative inflammatory response will be less and postoperative recovery faster if patients undergoing cardiac surgery receive washed red cells compared with standard care (unwashed red cells).

**Methods and analysis:**

Adult (≥16 years) cardiac surgery patients identified at being at increased risk for receiving large volume red cell transfusions at 1 of 3 UK cardiac centres will be randomly allocated in a 1:1 ratio to either red cell washing or standard care. The primary outcome is serum interleukin-8 measured at 5 postsurgery time points up to 96 h. Secondary outcomes will include measures of inflammation, organ injury and volumes of blood transfused and cost-effectiveness. Allocation concealment, internet-based randomisation stratified by operation type and recruiting centre, and blinding of outcome assessors will reduce the risk of bias. The trial will test the superiority of red cell washing versus standard care. A sample size of 170 patients was chosen in order to detect a small-to-moderate target difference, with 80% power and 5% significance (2-tailed).

**Ethics and dissemination:**

The trial protocol was approved by a UK ethics committee (reference 12/EM/0475). The trial findings will be disseminated in scientific journals and meetings.

**Trial registration number:**

ISRCTN 27076315.

Key questionsWhat is already known about this subject?Changes in allogenic red blood cells and the accumulation of toxic intermediaries in donor blood bags during storage are thought to contribute to the development of organ injury in transfusion recipients.Studies in animal models have suggested that removing the storage supernatant from allogenic red cells by mechanical cell washing may attenuate the inflammation and organ injury associated with transfusion.What does this study add?The objective of the REDWASH study is to determine whether mechanical washing of donor red cells will reduce inflammation and organ injury in adult cardiac surgery patients that receive large volume red cell transfusions.How might this impact on clinical practice?Mechanical red cell washing devices are widely used in cardiac surgery for the processing of shed autologous blood. If effective, this intervention could we widely adopted.

## Introduction

### The clinical problem

Cardiopulmonary bypass and other surgical techniques utilised in cardiac surgery are associated with a high incidence of organ injury and dysfunction that typically affects the kidney, heart and lungs.^1^ Organ injury affects up to 30% of all adult cardiac surgery patients and is associated with additional morbidity, high mortality and the increased use of healthcare resources.^2–5^ The underlying pathophysiological processes are poorly understood; there are no current interventions that have been shown to alter the natural history of these conditions and outcomes remain poor.^6–9^ As the population ages and increasingly elderly patients with more comorbidity are referred for cardiac surgery,^10^ it is likely that the risk of inflammatory organ injury will increase. Refining perioperative care to reduce the frequency and severity of inflammatory organ injury is therefore a clinical research priority.

### Blood transfusion and adverse outcome in cardiac surgery

Red cell transfusion is the preferred treatment for acute blood loss or the rapid reversal of anaemia in cardiac surgery patients. These indications are common, and red cell transfusion is also common, with over half of all cardiac surgery patients receiving red cells on average.^11^
^12^ However, red cell transfusion is strongly associated with adverse clinical outcomes including organ injury, infection and death.^13^
^14^ The clinical importance of these associations is uncertain. A recent meta-analysis of randomised trials has indicated that allogenic red cells may be beneficial in cardiac patients with severe anaemia.^15^ However, the volumes of red cells transfused for anaemia in these trial were small, typically 1–2 units, and there is uncertainty as to whether larger volumes of red cells, more commonly associated with severe bleeding, may have a different balance of risks and benefits. This is suggested by the much higher risk of mortality observed with large versus small volume transfusions in observational analyses (OR for death 1.73 and 2.68 for 1–2 units and 3–5, respectively^15^), and the much greater risk of death and organ injury in cardiac surgery patients that have been treated for severe blood loss.^16^ Observational studies cannot demonstrate causality however, and it is also not possible to randomise critically ill patients, many of whom are bleeding to red cell transfusion or no red cell transfusion. One approach to address this uncertainty is to modify red cells, to assess whether attenuation of the adverse effects of storage results in a reduction in adverse clinical outcomes. Intuitively, the benefits of these interventions would be greatest in recipients of large volume blood transfusion (LVBT). LVBT, defined as 4 or more units or greater than 1000 mL transfused^17^ is common, affecting up to 22% of patients in a 2010 audit of UK centres 22%, ranging from 8% to 45% between units.^11^ We have previously developed a preoperative risk score that can identify patients at risk of receiving LVBT with excellent discrimination.^17^ We will use this tool to identify an enriched cohort of patients that we believe may benefit most from our proposed blood safety intervention.

### The pathogenesis of transfusion-mediated organ injury

Organ injury and immunomodulation following transfusion have been attributed to the ‘storage lesion’; changes in red cell properties and accumulation of inflammatory particles in the supernatant of red cell units during storage.^18^ In experimental studies, we have shown that these changes cause inflammatory organ injury via complex mechanisms including platelet and monocyte activation, endothelial injury and oxidative stress and the loss of microcirculatory autoregulation.^19–22^ This results in paradoxical tissue hypoxia despite apparently adequate oxygen delivery, tissue inflammation, and organ dysfunction. The most important change that occurs in stored red cells appears to be the depletion of high energy phosphates in red blood cell (RBC) over time.^18^ This leads to the loss of autoregulatory function, erythrocyte deformability and changes in erythrocyte morphology that are associated with abnormal gas transfer and microcirculatory flow. A significant aspect of these changes is the overexpression of phosphatidylserine (PS) on the RBC surface attributable to diminished function of the ATP-dependent membrane-bound flippase enzyme that acts to maintain membrane asymmetry by transporting PS to the interior of the membrane and phosphatidylcholine to the exterior.^23^ High levels of PS expression are associated with rapid uptake of donor RBC by recipient myeloid tissue and hence diminished donor cell survival. They are also associated with the release of membrane vesicles from the erythrocytes during storage^24^ (figure 1).

**Figure 1 OPENHRT2015000344F1:**
[figure not shown]
Annexin V (AV) positive microvesicles (MV) in allogenic red cell stored in SAGM at 4°C for up to 42 days and after washing with a Fresenius Continuous AutoTransfusion System (CATS, Fresenius AG, Bad Homburg, Germany). SAGM, saline adenine glucose mannitol.

These microvesicles (MV) express high PS levels that have potent inflammatory effects.^25^ Our own research has indicated that MV levels increase progressively from the onset of storage, and that they may be removed by mechanical cell washing (figure 1). Furthermore, in a porcine model, we have shown that mechanical washing of allogenic RBC to remove these microparticles reduces inflammation and inflammatory organ injury in transfusion recipients (unpublished). In this study, washing cells that exhibited storage-related changes typical of human cells reversed platelet and endothelial activation and pulmonary injury in swine. On the basis of these results, we now hypothesise that the release of microparticles by erythrocytes during storage is associated with inflammatory organ injury in cardiac surgery patients receiving blood transfusion and that this may be prevented by red cell washing prior to transfusion. We propose to test this hypothesis in the current trial.

### Red cell washing

Red cell washing devices are ubiquitous in cardiac surgery. The salvage, washing, transfusion of *autologous* blood lost from the operative field is part of standard care, and has been shown to improve clinical outcomes, perhaps by reducing allogenic RBC exposure.^26^ Washing of *allogenic* RBC is also practiced in paediatric cardiac surgery. Low birthweight neonates and small infants are susceptible to the high ion (free haemoglobin, potassium, calcium) concentrations that are present in older RBC units and it is the practice in some centres to wash these using cell salvage devices prior to transfusion.^27^ A randomised controlled trial (RCT) of red cell washing in paediatric cardiac surgery patients failed to show a clinical benefit, although there was a reduction in measures of inflammation (interleukin (IL)-6:IL-10 ratios). Importantly, no adverse effects of this technique were reported in recipients.^28^

Standard cell saver devices use low speed centrifugation with resuspension in normalised saline without apparent detriment to human autologous or allogenic RBC.^29^
^30^ Our own studies (unpublished) have also documented significant homology between the effect of mechanical red cell washing using low speed centrifugation with the Fresenius Continuous AutoTransfusion System (CATS, Fresenius AG, Bad Homburg, Germany) and the washed red cells produced by the UK National Blood Service for patients at increased risk of hypersensitivity reactions. We suggest that the pretransfusion washing of stored donor cells using commonly used cell salvage devices at the bedside will offer a simple and practical blood safety intervention.

## Aims and objectives

The REDWASH trial will test the hypothesis that the severity of the postoperative inflammatory response will be less and postoperative recovery faster if patients undergoing cardiac surgery with cardiopulmonary bypass (CPB) who are at risk of large volume RBC transfusion receive stored allogenic RBC that are washed prior to transfusion when compared with standard care where stored RBC are administered without washing. A secondary hypothesis is that the adverse effects of transfusion are mediated by platelet and monocyte activation by microparticles within the storage supernatant and that by removing the supernatant this is attenuated.

Specific objectives of this trial are to:
Estimate mean differences in biochemical markers of the systemic inflammatory response between participants allocated to receive washed versus unwashed RBC.Estimate mean differences in hospital length of stay between participants allocated to receive washed versus unwashed RBC.Estimate differences in the frequency of inflammatory organ injury or death between participants allocated to receive washed versus unwashed RBC.Estimate the cost-effectiveness of washed versus unwashed RBC.Establish whether red cell washing attenuates postoperative platelet, endothelial cell and monocyte activation (mechanism substudy).

## Methods and analysis

### Study design

This study is a multicentre, single-blinded, parallel group RCT of washing of allogenic RBC prior to transfusion versus standard care (no washing).

### Study population and recruitment

The study will be carried out at three tertiary cardiac surgery centres in the UK: the University Hospitals of Leicester National Health Service (NHS) Trust, the Royal Victoria Hospital, Blackpool and University Hospitals Coventry and Warwickshire NHS Trust. These units perform over 3500 major cardiac procedures per year, of whom over 875 will be at risk of LVBT (from the UK National Audit of Blood Transfusion in Cardiac Surgery^11^). If red cell washing is effective, its clinical benefits and impact on resource use will be most apparent in patients at greatest risk of LVBTs. Patients at risk of LVBT will therefore be identified preoperatively using a risk score developed and validated by these investigators in a multicentre population.^17^

#### Inclusion criteria

Participant may enter study if ALL of the following apply:
Adult cardiac surgery patients (≥16 years) undergoing cardiac surgery with blood cardioplegia.Identified as representing a high-risk group for LVBT using a modified risk score. The score for inclusion ≥25. This has 55% positive predictive value for LVBT.^17^

#### Exclusion criteria

Participant may not enter study if ANY of the following apply:
Emergency or salvage procedure.Ejection fraction <20%, that is, very poor left ventricular function.Patients with end stage renal failure defined as an estimated glomerular filtration rate (eGFR) <15 mL/min/1.72m^2^ calculated from the Modification of Diet in Renal Disease equation,^31^ or patients who are on long-term haemodialysis or have undergone renal transplantation.Patients who are prevented from having blood and blood products according to a system of beliefs (eg, Jehovah's Witnesses).Patients with congenital or acquired RBC, platelet or clotting factor disorders (excluding those receiving antiplatelet therapy, warfarin or other systemic oral anticoagulants).Patient in a critical preoperative state (Kidney Disease: Improving Global Outcomes (KDIGO) stage 3 acute kidney injury (AKI)^32^ or requiring inotropes, ventilation or intra-aortic balloon pump) preoperatively.Pregnancy.Patients who are participating in another interventional clinical study.

### Intervention being investigated

#### Treatment regimens

Patients will be screened by the investigators to assess eligibility for entry into the study. Eligible patients undergoing cardiac surgery with CPB who consent to participate will be randomly allocated, in a 1:1 ratio to:
Group A: unwashed RBC (standard care);Group B: washed RBC.

#### Red cells

Allogenic RBC, harvested in citrate-adenine-phosphate-dextrose, buffy coat removed, leucocyte depleted, saline-adenine-glucose-mannitol stored red cell units, supplied by National Health Service Blood and Transplant as per standard practice will be used. For the intervention, each unit of RBC will be added to a continuous autotransfusion system (CATS, Fresenius AG, Bad Homburg, Germany), washed using a centrifugal method, as per the device instructions. The washed RBC will then be immediately administered to the patient as per standard practice. Washing may be impractical in bleeding patients where there is cardiovascular instability, and clinician discretion may lead to the administration of unwashed cells in the washed group in breach of protocol. The clinical indication and timing of every transfusion, and whether or not washing has occurred as indicated will be recorded. The haematocrit (Hct) threshold for transfusion will be 23. Clinician discretion may also allow variation in this threshold in certain situations, that is, bleeding, where Hct thresholds are impractical.

#### Administration of study treatment

RBC units (washed or unwashed) will be administered via the appropriate giving set, preferably 1 unit at a time. Before transfusion of washed or unwashed cells, the anaesthetist or intensive care unit (ICU) staff will check to ensure that the blood bag has the correct participant identification as per standard care. Because the washed RBC contains no additive solution, the washed RBC must be administered as soon as possible after its preparation. Cell washing and administration in the theatre and ICU will adopt policies as for the washing and transfusion of autologous blood; that is, after appropriate identification checks, the cells will be washed at the patient's bedside and administered immediately. Once washed, RBC units will not be stored for future use.

#### Deviations from protocol

In the event of any deviation from the trial protocol, defined as the administration of a washed unit to a patient randomised to the unwashed arm or vice versa, the deviation will be documented and the patient will continue to be treated according to the randomised allocation for all subsequent transfusions.

### Primary and secondary end points

#### Primary outcome

The primary outcome is serum IL-8 levels measured from venous blood samples taken at five postoperative time points; on return to intensive therapy unit (ITU), and 6, 24, 48 and 96 h, adjusted for baseline (preoperative) values. IL-8 levels reflect the severity of the systemic inflammatory response and are an important predictor of adverse clinical events in cardiac surgery patients.^33^
^34^ Our previous research^35^ has indicated that blood transfusion is associated with increases in the levels of this proinflammatory cytokine that are maximal between 4 and 24 h postoperatively (figure 2). However, the intervention period in the REDWASH trial extends to 48 h postsurgery and therefore IL-8 levels will be measured up to 96 h to capture events after this point.

**Figure 2 OPENHRT2015000344F2:**
[figure not shown]
Individual patient data meta-analysis showing serial interleukin (IL)-8 levels measured up to 48 h postsurgery in transfused and non-transfused patients from historical data.

#### Secondary outcome

The secondary outcome measures are listed in table 1.

**Table 1 OPENHRT2015000344TB1:** Secondary outcomes

Outcome	Definition/method of verification
Inflammatory organ injury, sepsis or death	▸ Sepsis will be defined as antibiotic treatment for suspected infection, *and th*e presence of SIRS within 24 h prior to start of antibiotic treatment where SIRS is defined as ≥2 of the following conditions: temperature >38^o^C or <36^o^C; heart rate >90 bpm; respiratory rate >20 breaths/min or PaCO_2_ <32 mm Hg; white cell count >12 000/mm^3^ or <4000/mm^3^, *or* antibiotic treatment for wound infection.^36^ ▸ Acute kidney injury, defined as KDIGO^32^ stage 1, 2 or 3. ▸ Acute lung injury, defined as PaO_2_/FiO_2_ ratio <300 mm Hg or a requirement for respiratory support; invasive ventilation>48 h, non-invasive ventilation>4 h, reintubation, tracheostomy, or ARDS.^37^ ▸ Low cardiac output, defined as new intraoperative or postoperative intra-aortic balloon pump insertion OR a cardiac index of <2.2 L/min/m^2^ measured using a Swann Ganz catheter that is refractory to appropriate intravascular volume expansion after correction or attempted correction of any dysrhythmias, OR the administration of inotropes including dobutamine, enoximone, milrinone, levosimendan and adrenaline. ▸ Death. ▸ Differences in Multiple Organ Dysfunction Score^38^ at days 1, 2, 3 and 5.
Bleeding and transfusion	▸ Measured blood loss in drains at 6 h postoperatively. ▸ The number of units of RBC and other blood components transfused during the operative period and postoperative hospital stay will be recorded. ▸ Age of each unit of RBC transfused. ▸ Serial haemoglobin levels/haematocrit.
Transfusion reactions	▸ Febrile transfusion reactions. ▸ Non-haemolytic transfusion reactions. ▸ Haemolytic transfusion reactions. ▸ As defined in http://www.shotuk.org/wp-content/uploads/SHOT-Definitions-Jan-2015.pdf
Other clinical outcomes	▸ Stroke; diagnosed by brain imaging (CT or MRI), in association with new onset focal or generalised neurological deficit (defined as deficit in motor, sensory or coordination functions). ▸ ST elevation myocardial infarction accompanied by troponin I >5000 pg/mL.
Hospital stay, cumulative resource use and quality of life	ICU, HDU and hospital length of stay will be determined by the assessment of care level. Resource use will be costed using credible nationally published sources. Postdischarge resource assessed using a Health Resource Use Questionnaire at 6 weeks and 3 months postsurgery. Quality-adjusted life years assessed using the EuroQol EQ-5D^39^ questionnaire at baseline and at 6 weeks and 3 months postsurgery.
Compliance with the washing protocol	Data will be collected for all patients during surgery to characterise compliance with the randomly assigned washing protocol.
Additional markers of inflammation and organ injury will be assessed in a mechanism substudy in the first 60 consecutive patients recruited at Glenfield Hospital	▸ Urinary LFABP, NGAL at baseline and at 6, 12 and 24 h.^40^ ^41^ ▸ Serum troponin I at baseline and at 24 and 48 h. ▸ Platelet aggregation (Multiplate) in the first 48 h. ▸ Transfused RBC characteristics (washed and unwashed); ATP levels, 2,3DPG, deformability, osmotic fragility, cytokine levels. ▸ Serum levels of GM-CSF, IFN-γ, IL-1β, IL-2, IL-4, IL-5, IL-6, IL-10 and TNF-α at the same time points as for the primary end point. ▸ Platelet and monocyte activation as determined by flow cytometry for a subgroup of patients. ▸ Endothelial injury as determined by quantification of endothelial-derived microparticles by flow cytometry. ▸ Effect of blood harvested from recipients on platelet and monocyte activation within a microfluidics system.

ARDS, adult respiratory distress syndrome; FiO_2_, fractional inspired oxygen; GM-CSF, granulocyte-macrophage colony-stimulating factor; HDU, high dependency unit; ICU, intensive care unit; IFN, interferon; KDIGO, Kidney Disease: Improving Global Outcomes; LFABP, liver fatty acid binding protein; NGAL, neutrophil gelatinase-associated lipocalin; PaCO_2_, arterial carbon dioxide tension; PaO_2_, arterial oxygen tension; RBC, red blood cell; SIRS, systemic inflammatory response syndrome; TNF, tumour necrosis actor.

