### Research procedures

#### Screening and eligibility assessment

The patients risk score will be calculated at the preoperative assessment clinic or from our standard in patient referral protocols that include detailed clinical and demographic information (table 2). An information leaflet, approved by the local Research Ethics Committee, will be sent to all potentially eligible patients waiting at home with the letter giving a date for their operations. Each patient will have at least 24 h to consider whether to participate or not. In a few cases, this time interval may be as little as 12 h, for example, for patients admitted for urgent surgery without prior notification to the waiting list coordinator. Despite the short notice, it is important to include these patients for the applicability of the trial findings since about 40% of patients having cardiac surgery are admitted as urgent cases, and these are often those at greatest risk for LVBT. Written informed consent will be obtained at the time of admission. Details of all patients approached for the trial and reason(s) for non-participation (eg, reason for being ineligible or patient refusal) will be documented.

**Table 2 OPENHRT2015000344TB2:** Key data collection points

	Preoperation	Operation day	Day 1	Day 2	Day 3	Day 4	Discharge	6 weeks	3 months
Eligibility	✓								
Written consent	✓								
Randomisation	✓								
EQ5D Questionnaire	✓						✓	✓	✓*
Bloods: serum biochemistry (creatinine and troponin T/I)	✓†	✓† (CICU and 6–12 h)	✓† (24 h)	✓† (48 h)	✓† (72 h)	✓‡ (96 h)	✓‡		
Bloods: serum inflammatory biomarkers	✓†	✓† (CICU and 6–12 h)	✓† (24 h)	✓† (48 h)	✓† (72 h)	✓‡ (96 h)	✓‡		
Bloods: full blood counts	✓	✓ (CICU and 6–12 h)	✓ (24 h)	✓ (48 h)	✓ (72 h)	✓‡ (96 h)	✓‡		
Bloods: plasma sample for MP analysis and monocyte activation	✓	✓ (CICU)	✓ (24 h)	✓ (48 h)					
Urine sample and volume: NGAL, urea and elecrolytes	✓	✓ (6 and 12 h)	✓ (24 h)	✓†§ (48 h)					
Operative details		✓†							
Clinical outcomes						✓	✓	✓¶	
Serious adverse event monitoring		✓	✓	✓	✓	✓	✓	✓¶	
Resource use data							✓	✓¶	✓*
Bloods: platelet response**	✓**	✓** (CICU and 6–12 h)	✓** (24 h)	✓** (48 h)					

*Indicates data collection via postal questionnaire.

†Indicates samples taken as part of normal care.

‡Discharge time point if hospital stay exceeds 5 days.

§Indicates sample for determination of routine urea and electrolytes only.

¶The 4–6-week time point in accordance with normal postoperative care.

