#### Trial-specific tests and procedures

Participants will undergo the following tests and procedures as part of the research.

*Urine samples* will be collected on the day before surgery, on the day of surgery (6 and 12 h postsurgery) and day 1 (24 h postsurgery) for the measurement of AKI biomarkers.

*Blood samples* will be collected from all participants in the trial at the following time points: preoperatively, postoperatively, on return to ITU, 6–12 h postoperative, 24 h postoperative, 48 h postoperative, 72 h postoperative, 96 h postoperative or hospital discharge, whichever is the earliest (ie, seven blood samples will be taken per patient). Inflammatory markers in serum; granulocyte-macrophage colony-stimulating factor (GM-CSF), interferon-γ, IL-1β, IL-2, IL-4, IL-5, IL-6, IL-8, IL-10 and tumour necrosis factor-α will be measured on the MagPix Multiplex platform (Luminex Corp). Preoperatively, on return to cardiac Intensive care unit (CICU) and 24 and 48 h postoperative, additional blood will be collected for analysis of MP levels and platelet and monocyte activation using flow cytometry (Beckman Coulter MCL-XK, High Wycombe, UK) and multiplate impedance electrode aggregometry (Roche, Rotkreuz, Switzerland).

Urine and blood samples will be transferred to the central laboratory where they will be stored until analysed for cytokines, coagulopathy, inflammatory cell activation, endothelial injury and inflammatory organ injury biomarkers. The samples will be kept until the completion of the study. Left over material may be used for future research with permission of the research participants. Full blood count analysis will be conducted at the local haematology laboratories of the participating sites.

*Assessment of cumulative resource use and utility* will be carried out for all participants: Utility will be assessed using the EuroQol EQ5D^39^ assessed at baseline, 6 weeks (routine clinic visit) and 3 months after surgery (postal questionnaire). Hospital resource use will be directly measured using available reference costs.^43^ Postdischarge resource use will be assessed using a health resource usage questionnaire conducted at 6 weeks (routine clinic visit) and 3 months after surgery (postal questionnaire) as previously described.^36^

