#### Measures taken to avoid bias

All necessary steps will be taken to reduce the risk of bias.^44^
^45^ The trial will be analysed on an intention-to-treat basis, that is, outcomes will be analysed according to the treatment allocation, irrespective of future management and events, and every effort will be made to include all randomised patients. Selection bias will be minimised by concealed randomised allocation. As the intervention utilises a large piece of bedside equipment, the autotransfusion device, it will be impossible to blind clinical staff and patients to the intervention. Detection bias will be minimised, however, by blinding of laboratory staff analysing cytokines, biomarkers and inflammatory processes. Specifically, urine and serum samples obtained exclusively for the trial will be identified only by a trial acronym, patient’ study ID, initials and date of birth, and the time at which the sample was taken, ensuring that laboratory staff performing analyses are blinded. Detection bias for the clinical outcomes will also be minimised by the use of objective outcome criteria; as defined in the Outcome section above. Staff recording components of the secondary outcome (any inflammatory injury, sepsis or death) at the time of discharge will be blinded to further minimise the risk of detection bias. Blood and other urine samples, that are also obtained as part of routine care will be analysed routinely in NHS laboratories by personnel who are unaware that the participant is in a trial. Decisions about discharge from ICU, HDU and from hospital will be made by clinical staff on the basis of existing institutional protocols. ICU/HDU transition will be defined as transition from level 3 (1:1 nursing ratio) to level 2 (1:2 nursing ratio). HDU/ward transition will be defined as time of arrival on the ward. In order to minimise attrition bias, we aim to include data for all randomised participants in the data analyses.

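### The infarction outcome is defined on troponin I alone, but the all-patient schedule accepts troponin T or I, so a participant with only a troponin T result could not be classified as having the event

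*Protocol article*

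**What the plan says.** In Table 1 of the protocol article (Secondary outcome), under other clinical outcomes, infarction is defined as "ST elevation myocardial infarction accompanied by troponin I >5000 pg/mL". That is one analyte with one absolute cut-off, and no alternative biochemical criterion.

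Table 2 (Screening and eligibility assessment) lists the all-patient troponin measurement in the row "Bloods: serum biochemistry (creatinine and troponin T/I". From the preoperative sample to 72 h the entries in that row carry a dagger, which the footnote explains as "Indicates samples taken as part of normal care".

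Troponin I is named as a trial measurement in one other place, again in Table 1: "Serum troponin I at baseline and at 24 and 48 h". That entry belongs to the "mechanism substudy in the first 60 consecutive patients recruited at Glenfield Hospital".

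Three further statements bear on which assay a participant would have:

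- Study population and recruitment: "The study will be carried out at three tertiary cardiac surgery centres in the UK". No site's troponin assay is given.
- Measures taken to avoid bias: "Blood and other urine samples, that are also obtained as part of routine care will be analysed routinely in NHS laboratories".
- Trial-specific tests and procedures: "Urine and blood samples will be transferred to the central laboratory where they will be stored until analysed". The analyses listed there include biomarkers of inflammatory organ injury.

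**The concern.** The schedule accepts a measurement that the outcome definition cannot use. The cut-off is an absolute troponin I concentration, so a troponin T result cannot be compared with it, however high the result is. Read literally, a participant with new ST elevation and only a troponin T result would be recorded as having no infarction.

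The Statistical analyses section says that specific morbidities are too infrequent for a comparison between groups and that their frequencies will be tabulated. The Frequency of analysis section sends outcome data, by group, to the monitoring committee every six months. In a table of rare events, the loss of even a few changes what readers and the committee see. What is at stake is the completeness of one line in that table and whether it means the same thing at every site.

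**Working it through.** The plan gives no figure to reproduce, and no power or sample-size calculation depends on this point. The check compares the outcome definition with the measurements scheduled.

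**Step 1. What the definition needs.** Table 1 needs ST elevation and a troponin I value above 5000 pg/mL. No troponin T threshold or conversion rule appears anywhere in the article.

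**Step 2. What the schedule guarantees.** Table 2 guarantees troponin T or troponin I. On the natural reading, a site that reports only T complies with the schedule.

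**Step 3. Who is assigned troponin I by name.** Only the substudy participants are, at three time points.

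- Planned total: 170 (Statistical analyses).
- Substudy: 60 (Table 1 and Plan of analysis).
- Assigned troponin I by name: 60/170 = 35%.
- Left to the T or I row: 170 − 60 = 110, and 110/170 = 65%.

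**Step 4. Range of participants affected.** If every site in fact measures troponin I, 0 participants are affected. If every participant outside the substudy has troponin T only, about 110 are. The article gives nothing to narrow this range. The upper end assumes that the substudy fills to 60 and that its three troponin I samples are enough to classify its members.

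**Step 5. Is the assay settled elsewhere?** It is not.

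- The dagger does not settle it. The serum inflammatory biomarker row carries the same dagger, yet those markers are measured for the trial on a multiplex platform. The dagger therefore describes how the sample is drawn and not which assay is run or where.
- The statement on NHS laboratories makes local analysis plausible but does not say which troponin any laboratory reports.
- Central storage makes a later troponin I assay possible, but no sentence commits the trial to one outside the substudy.

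**Step 6. Direction of the error.** Randomisation is stratified by study site, so a site measuring only T would contribute to both arms in roughly equal numbers. The expected effect is under-counting in both arms, not a systematic difference between them.

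**The case against.** The strongest reply is that nothing in the article shows that any event would be lost. No site is said to use troponin T, and the schedule's wording is compatible with troponin I at all three. Trial serum is held centrally, so a missing troponin I could still be obtained. Site-specific cut-offs are also the kind of detail that an article leaves to the full protocol or a laboratory manual.

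Much of this stands, and it rules out several stronger readings.

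- **That infarctions at some site can never be counted.** This needs a site that measures T alone and no later assay of stored serum. The article states neither.
- **That a particular number of events will be missed.** This needs an event rate, each site's assay and each site's recruitment. The article supplies none of these.
- **That the trial would give false reassurance about cardiac harm.** The Adverse events section has serious adverse events notified by the other two sites and adverse events collected through the hospital stay and the three-month follow-up. That reporting does not depend on the troponin cut-off.
- **That the economic analysis inherits an under-count.** It collects resource use, complications and their treatment, and the article does not restrict complications to events meeting the Table 1 definition.

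The point about condensation does not dispose of the finding. The absence of a troponin T cut-off would not by itself be a finding. Here, however, the definition is written out in Table 1, and it does not fit the measurement written out in Table 2 of the same article.

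**Conclusion.** The inconsistency is real and its consequence is conditional. As written, the definition cannot classify a participant whose only result is troponin T, although the schedule accepts that result. If a site measures only troponin T, and troponin I is not obtained in some other way, infarctions there would be under-counted in both arms.

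Between 0 and about 110 of 170 participants could be affected, and the number of missed events cannot be derived from the article. Only one infrequent, tabulated secondary outcome is touched. The primary IL-8 outcome, the sample size and the composite of organ injury, sepsis or death do not use this definition. The point is worth correcting because the correction is cheap, but it does not threaten the trial's main conclusions.

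**What to change.** Reconcile Table 1 with Table 2 before outcome data are reviewed by group. Either of two routes would do:

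1. **Secure troponin I.** State that troponin I is measured for all participants at all sites. A smaller version is to run it on stored trial serum for any participant with new ST elevation and no troponin I result. The cost is a few extra assays.
2. **Prespecify a troponin T criterion.** State, for each assay in use, what counts towards the outcome. The cost is one line in Table 1. The drawback is that T and I cut-offs are not perfectly equivalent, so events classified on different assays are not strictly the same event.

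Whichever is chosen, apply the rule identically in both arms and report the assay used beside the tabulated frequencies.
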